### ***In the community***

These are mainly qualitative surveys to assess the degree of acceptance of the reduced dose of RUTF by the community. To achieve this, FGs, in-depth interviews and field observations will be carried out:

- ***Focus groups***: they will bring together an average of 8 people and will last between 45 minutes to an hour. Participants in FG will be accompanying children participating in the study. The drawing of lots will be carried out among those accompanying the last children followed. In each ZS, 3 focus groups will be carried out, one with the mothers, one with the fathers and one with the young people.
- ***In-depth interviews***: will mainly concern key informants including politico-administrative authorities, traditional authorities (village chief) healthcare providers (nurses from UNTAs), the two head doctors of ZS, healthcare providers (due to a nurse by UNTA selected ) and community leaders (depending on their influence, 3 community leaders will participate per ZS).
- ***Field observations***: they will be carried out in the UNTAs, households of participants, markets and other strategic places of the corresponding ZS.

Triangulation of sources and methods will be used to improve data quality.

At the end of the FG, in-depth interviews and field observation, the reports of the day's progress, the notes taken as well as the recordings will be sent to the investigators.

The practical modalities and the tools to be used are given in the appendix to this protocol (appendix 4).

### **2.3.2. Data management**

The data will be collected on individual UNTA files by the IT then by double entry for 10% of the files, they will be recorded on tablets by the data entry officers recruited for the study. The principal investigator will regularly analyze the data collected after it has been sent to the central server and will provide feedback to the data collectors on the inconsistencies observed.

The principal investigator, the data entry agents under the supervision of the scientific manager, will have to check the quality of the data on a daily basis and provide feedback to the ACF supervisors and IT via the Research Program Manager for any corrections on the site.

Only the principal investigator and the Research Program Manager will have free access to the data during the study. The latter two are responsible for extracting the database from the server, making it anonymous and sharing it for statistical analysis.

### **2.3.3. Statistical analyzes**

For the quantitative part of the study, the data will be summarized in Mean and Standard Deviation if they are normally distributed (normality test) for continuous variables and in absolute and relative frequencies for categorical variables.

The t-test and the chi-square test will be used respectively to compare the means and the proportions of the socio-demographic characteristics at admission for the quantitative and qualitative variables.

Linear regression analyzes will be used to determine the significant differences between the 2 groups of children for the quantitative variables.

Binary logistic regression analyzes will be used to determine the significant differences between the 2 groups of children for the binomial qualitative variables (2 response modalities).

Multinomial logistic regression analyzes will be used to determine the significant differences between the 2 groups of children for the multinomial qualitative variables (3 or more modalities).

All analyzes will be done in an adjusted and unadjusted model and a difference is statistically significant when the P-value is less than 0.05.

The results will be analyzed using statistical software, in this case STATA, version 17.

The main analyzes will be done by intention to treat (ITT) and per protocol for the main result, in this case, the speed of weight gain. The other secondary results will be analyzed only by intention to treat (ITT).

For the DPM, a score will be assigned to the participant and the sum will constitute the total score for each participant per domain.

For focus group data, after transcription of the recordings into Word 2019, thematic analysis will be done using Excel tables (matrix) or Nvivo® software.

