### **b. Modification or interruption of the intervention**

During the implementation of this study, the intervention will be interrupted for each participant who presents (12):

- Withdrawal of informed consent;
- Discontinuation of treatment;
- Lost view ;
- Failure to process.

Chart 3 : Criteria for leaving the study outside of the cure

| Criteria                                        | Definition                                                                                                                                                       |
|-------------------------------------------------|------------------------------------------------------------------------------------------------------------------------------------------------------------------|
| Abandonment-confirmed                           | Patient absent for two consecutive weeks (declared abandonment in the third) sought by the RECOs and confirmed as having abandoned                               |
| Unconfirmed abandonment                         | Patient absent for two consecutive weeks (declared abandonment in the third) but his actual method of discharge (abandonment or death) not having been confirmed |
| Death                                           | Participant whose death has been certified by a nursing staff                                                                                                    |
| Lost view                                       | Change of address, followed in another CS outside the study area                                                                                                 |
| Treatment failure                               | Referred to UNTI following the appearance of danger signs (temporary discharge *)                                                                                |
| Withdrawal of consent                           | Any time after randomization                                                                                                                                     |
| Non-response to treatment (even if very rarely) | Children who do not recover after 12 weeks of treatment                                                                                                          |

*\*AT their return the children of the arm with reduced dose will resume with the dose planned for the week in which they were transferred, so they do not restart the treatment from zero but continue it.*

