##### b. Additional results

The additional results expected in this study, in the two groups (control and intervention), are:

- **The duration of the edema melting:** calculated in number of days, this indicator corresponds to the time taken for the lower limbs of SAM children to return to their normal volume. The expected result is the onset of melting of the edemas within the first 14 days after admission and their complete disappearance after 21 days of treatment.
- **The length of stay:** calculated in number of days, this indicator corresponds to the time elapsed between admission and discharge ( $PB \geq 12.5\text{cm}$  and / or  $PT \geq -3$  Z score and / or edema melt). The maximum length of stay is 12 weeks or 3 months(12).
- **The cure rate:** A child will be considered cured if he meets the cure criteria according to his admission category: A  $PT \text{ index} \geq -1.5$  or  $PB \geq 125 \text{ mm}$  during two consecutive visits and no edema during two visits (2 consecutive weeks).
- **The dropout rate:** it is the proportion of children confirmed alive who missed two successive visits. The abandonment is confirmed once after the visit of the RECO which confirms that the child is alive despite his 2 absences during the weekly visits. Children who have abandoned will be followed up to 3 months after the abandonment. For children who can be found, offer the caregivers a small snack at the single appointment 3 months after abandonment to take the anthropometric measurements.
- **Death rate :** the proportion of children randomized to the study who died during the intervention at any time.
- **Cost savings** (average cost saved and cost saved per child treated): this involves comparing the cost of treatment for children in care and declared cured in the two groups. We will use a societal perspective including the direct costs of drugs and RUTF

(purchase, transport, transport and storage) to assess the cost for each child, the HR costs involved in the care, the non-medical costs (food and transport. beneficiaries), indirect costs (loss of productivity).

- The growth velocity of the anthropometric variables and indices: it will be a question of evaluating the prevalence of stunting, underweight of the children included in the study in the two groups at the end of the treatment.

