| Evaluate the duration of treatment for each participant in the two groups                    | Duration of the treatment                    | Time between admission and discharge (PB≥12.5cm or PT ≥-3 Z score or edema melt)                                                                                                         | number of days           | interval |
| Assess dropout, cure, treatment failure and mortality rates                                  | Dropout rate in each arm                     | Number of children who have abandoned treatment and who no longer come to the center even after 3 home visits / total of children followed in each arm                                   | percentage               | interval |
|                                                                                              | Recovery rate                                | Percentage of children having reached the discharge after 3 months of treatment                                                                                                          | percentage               | interval |
|                                                                                              | Proportion Transfer to hospital in each arm  | Number of children being transferred to hospital during treatment (3 months) following a medical complication or if stagnation or loss of appetite / total children followed in each arm | percentage               | interval |
|                                                                                              | Proportion of Deaths in each arm             | Number of children who died during the stay at UNTA or during transfer to UNTI / total child followed in each arm                                                                        | percentage               | interval |
| Evaluate the cost and savings made with a reduced dose of RUTF compared to the standard dose | % savings in SAM treatment with reduced dose | Difference in cost between treatment with standard dose and treatment with reduced dose, expressed in%                                                                                   | percentage               | interval |

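### Length of stay is a capped, interrupted time to recovery, but the protocol compares it by linear regression under ITT; unequal early exit between arms would then pass for a difference in speed of recovery

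*Protocol*

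**What the plan says.** Protocol 2.1.4, b. Additional results, measures length of stay in days: "calculated in number of days, this indicator corresponds to the time elapsed between admission and discharge". It adds a ceiling: "The maximum length of stay is 12 weeks or 3 months". Annex 8 lists treatment duration as a number of days on an interval scale, defined as "Time between admission and discharge (PB≥12.5cm or PT ≥-3 Z score or edema melt". Duration of oedema melting is also in days.

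Chart 3 (2.1.3, b. Modification or interruption of the intervention) lists the ways of leaving other than cure. They include default ("Patient absent for two consecutive weeks (declared abandonment in the third) sought by the RECOs and confirmed as having abandoned"), death ("Participant whose death has been certified by a nursing staff"), loss to view, withdrawal of consent, and non-response ("Children who do not recover after 12 weeks of treatment").

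Section 2.3.3 fixes the method: "Linear regression analyzes will be used to determine the significant differences between the 2 groups of children for the quantitative variables". For the analysis set it says "The other secondary results will be analyzed only by intention to treat (ITT"). No censoring, competing-event or time-to-event method appears in the protocol. Equal length of stay in the two arms is one of the stated secondary hypotheses.

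**The concern.** A regression on days compares mean observed stay. That equals mean time to recovery only if every child is followed to recovery, and here many will not be. A child still unrecovered at 12 weeks would enter as 84 days. A child who defaults in week 3 either enters as about three weeks, like a very fast recovery, or has no value and drops out of an analysis declared to be ITT.

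This is not a detail left to a statistical analysis plan. The protocol itself names the method and the analysis set, and a later plan that followed them would carry the problem forward. At stake is the claim that the reduced ration does not prolong treatment. If the reduced-dose arm loses more children, the error favours the reduced dose.

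**Working it through.** **The plan's own figure.** There is none for length of stay. The 335 per group in 2.1.6 is for weight gain; it reproduces (one-sided 5%, 80% power, SD 2.6, margin 0.5) but does not bear on this point.

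**Inputs.** From the documents: cap of 84 days; 500 children per arm (Annex 5); in the earlier Burkina Faso trial, median treatment 56 days, IQR 35-91 (section 1.1). Assumed, because the documents give nothing by arm: exit rates and their timing, and the shape of the recovery distribution.

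**Illustration 1.** Time to recovery is log-normal with log-SD s = 0.5. Children assigned to default leave uniformly over days 7-42: 10% in the standard arm, 20% in the reduced arm.

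Step 1, capped mean without default, with m the median and c = 84:
M = m·exp(s²/2)·Φ((ln(c/m) - s²)/s) + c·[1 - Φ(ln(c/m)/s)]
- m = 56: 63.46 × 0.622 + 84 × 0.209 = 57.0 days
- m = 60: 67.99 × 0.569 + 84 × 0.251 = 59.7 days
- True delay: 59.7 - 57.0 = +2.7 days

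Step 2, mean observed stay with default fraction p. The mean stay d of those assigned to default is about 24 days, just under the midpoint of 24.5 because a few recover first:
mean = (1 - p)·M + p·d
- Standard, m = 56: 0.9 × 57.0 + 0.1 × 23.9 = 53.7
- Reduced, same recovery: 0.8 × 57.0 + 0.2 × 23.9 = 50.4; difference **-3.3 days** although recovery is identical
- Reduced, m = 60: 0.8 × 59.7 + 0.2 × 24.0 = 52.6; difference **-1.1 days** against a true +2.7

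Step 3, recovered children only (simulated): 51.06 - 49.61 = **+1.45 days** against a true +2.7. With identical recovery the difference is about -0.3 days.

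With log-SD about 0.71, which matches the IQR of 35-91 [(ln 91 - ln 35)/(2 × 0.6745)], the m = 60 case gives -1.5 observed against +2.2 true.

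**Illustration 2.** Log-normal recovery with median 56 and IQR 35-91; exits at a constant rate, set to give the stated percentages; reduced minus standard, in days:

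| Recovery on reduced dose | Exits, standard v reduced | True difference | All observed stays | Recovered only |
|---|---|---|---|---|
| identical | 10% v 10% | 0 | 0.0 | 0.0 |
| identical | 10% v 15% | 0 | -1.7 | -0.4 |
| identical | 10% v 20% | 0 | -3.6 | -0.8 |
| 10% slower | 10% v 10% | +3.0 | +2.9 | +1.8 |
| 10% slower | 10% v 20% | +3.0 | -0.7 | +1.0 |

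For -3.6 days (SD 25.2), the standard error is 25.2 × √(2/500) = 1.59, so z is about 2.2 and the chance of P < 0.05 is about 61%, with no difference in recovery.

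With equal exits there is no spurious difference and no reversal. A real delay still shrinks, slightly if all stays count (2.9 for 3.0) and more if only recovered children count (1.8 for 3.0), because slow recoveries beyond 84 days drop out of the comparison.

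**The case against.** Several stronger readings are tempting, and the documents do not support them.

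- **That the protocol counts a default as a recovery.** It does not say so. Counting observed days is the natural ITT reading, but both definitions put recovery-type criteria in brackets after discharge, and a defaulter may meet none of them. On the recovered-only reading the sign in Illustration 1 stays right (+1.45). If exits are excluded but non-responders are kept at 84 days, the difference is about +2.5 against +2.7, so nearly unbiased, though no longer ITT. Sign reversal therefore belongs to one reading only.
- **That the reduced arm will lose more children.** Section 2.2.4 says only that parents may deduce the dose, and the interview guides merely ask about abandonment. Dosing is also identical in weeks 1-2. If the extra ten points of default start at day 15, their mean exit day moves from 24.5 to 28.5, and -1.1 becomes -1.1 + 0.10 × 4 = -0.7.
- **That the cost comparison inherits the bias.** It does not. Annex 5, 3.2.2, costs the follow-up visits actually made, for which stay up to default is the relevant quantity.
- **That oedema melting is shown to be biased.** It has the same structure, but no size has been worked out, and the protocol expects oedema to be gone by about day 21, largely under identical dosing.

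It is also fair that -1.1 days lies within noise (standard error about 1.4), and that cure, default and death are reported by arm, so a large imbalance in losses would be visible. In Illustration 1 with m = 60, cure is about 72% v 61%. That helps a careful reader but does not make the regression on days a valid test of equal time to recovery.

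**Conclusion.** The point holds in this form: linear regression under ITT does not validly compare length of stay as a measure of recovery, because stay is capped and interrupted and unrecovered children have no defined value. Counting observed days rewards the arm that loses more children, by about 1.7 days per five-point excess of exits in both illustrations (0.05 × (57.0 - 23.9) = 1.7). Counting only recovered children departs from ITT and cuts a true delay by about half in Illustration 1.

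These sizes rest on assumed exit rates, exit timing and a log-normal recovery time. A spurious difference, or a reversal, requires exit rates that differ by arm. The outcome is secondary, and the point does not touch the weight-gain conclusion. It should be corrected before analysis.

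**What to change.** First reconcile the event. For discharge, 2.1.4 b uses PT ≥ -3 under length of stay but PT ≥ -1.5 under cure, and Annex 8 repeats ≥ -3. Until these passages agree, recovery is not defined.

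Then, in 2.3.3, replace linear regression for this hypothesis with time to recovery in all randomised children:
- cumulative incidence of recovery, with death and default as competing events;
- loss to view and withdrawal censored at the last visit, non-recovery censored at 12 weeks;
- the clock kept running through a UNTI transfer, which Chart 3 treats as temporary;
- the arm difference in 12-week cumulative incidence and median days to recovery, with 95% CI, plus a Fine-Gray or cause-specific Cox model stratified by UNTA.

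Default then lowers an arm's recovery curve instead of making it look faster. The 12-week value largely repeats the cure rate; the curve and median add the timing. Observed days of stay can remain as a descriptive measure of resource use. Use the same approach for oedema resolution in children admitted with oedema.

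The cost is analysis wording: weekly visits and exit categories are already recorded. The small downside is a cumulative-incidence or hazard measure to explain beside mean days.

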#### **b. Specific objectives**

##### **Primary objective**

To assess the effectiveness of a reduced dose of RUTF in the management of SAM in children aged 6 to 59 months on the rate of weight gain (g / kg / d) from admission to discharge .

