## **Research hypotheses**

### **Main hypothesis**

Children receiving the reduced dose will have the same weight gain from admission to discharge as children receiving the standard dose of RUTF with a non-inferiority margin of 0.5g / kg / day.

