#### 2.1.4.Results

##### a. Main result

The main outcome of this study will be the velocity of weight gain for each participant in the two study groups (control and intervention group). The acceptable weight gain is 5 g / kg / day for each participant regardless of the group to which he belongs. This weight gain is an average calculated between the gain on admission and on discharge for all the children admitted to the study (intention to treat) and then only for those who are declared cured (per protocol).

To conclude that there is no inferiority, it is assumed that the reduced dose will not be less than the standard dose if the difference in weight gain is less than 0.5 g / kg / day. Therefore, participants in the intervention group should not show a weight gain <4.5 g / kg / day to conclude that the reduced dose of RUTF was not inferior.

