## **2.2. Randomization**

### **2.2.1. Sequence generation**

Randomization by blocks of variable size will be used in this study in each of the 14 UNTAs. In order to ensure that the participants are evenly distributed, in each block there will be the same number of children from each group(41) (42).

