## Annex 8: List of variables according to specific objectives

| Specific objectives                                                                                                                                                                                                                                                                                                                 | Variables                                   | Definition                                                                                                                 | Values                                                                                | Ladder   |
|-------------------------------------------------------------------------------------------------------------------------------------------------------------------------------------------------------------------------------------------------------------------------------------------------------------------------------------|---------------------------------------------|----------------------------------------------------------------------------------------------------------------------------|---------------------------------------------------------------------------------------|----------|
| Primary objective                                                                                                                                                                                                                                                                                                            |                                             |                                                                                                                            |                                                                                       |          |
| Evaluate, on an outpatient basis, without additional staff to collect data and in a food insecure situation, the effectiveness of a reduced dose of RUTF in the management of SAM with edema in children aged 6 to 59 months over the rate of weight gain (g / kg / d) of children aged 6 to 59 months from admission to discharge. | PB                                          | Measurement of the Circumference of the arm halfway between the acromion between the olecranon in cm                       | Normal: $\geq 12.5$ cm
MAS: $< 11.5$ cm
MAM: $\geq 11.5$ and $< 12.5$ cm        | interval |

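### The primary weight-gain comparison is run in an adjusted and an unadjusted model of equal standing, and the unadjusted one omits the 14 UNTAs within which randomisation is blocked

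*Protocol*

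**What the plan says.** Protocol section 2.3.3 gives the method for continuous outcomes: "Linear regression analyzes will be used to determine the significant differences between the 2 groups of children for the quantitative variables". It then sets a general rule: "All analyzes will be done in an adjusted and unadjusted model and a difference is statistically significant when the P-value is less than 0.05". The primary outcome, velocity of weight gain, is continuous, so both sentences apply to it. The same section adds that "The main analyzes will be done by intention to treat (ITT) and per protocol for the main result". No covariates are listed for the adjusted model, and neither model is called primary.

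The non-inferiority criterion stands elsewhere. The main hypothesis compares the arms "with a non-inferiority margin of 0.5g / kg / day", and section 2.1.4 (a. Main result) accepts non-inferiority "if the difference in weight gain is less than 0.5 g / kg / day". Neither place ties the criterion to a model or to a confidence limit.

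On design, section 2.2.1 states: "Randomization by blocks of variable size will be used in this study in each of the 14 UNTAs". Section 1.3 and the executive summary also place randomisation within each UNTA.

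**The concern.** Two regressions of the same outcome give two estimates and two standard errors. Near the margin, one can support non-inferiority while the other does not. The protocol gives both equal standing, so it does not say what the trial would then conclude, and the choice could be made after results by arm are known. The only criterion written beside the two models is P < 0.05 for a difference. That is not a test against a margin, so it cannot settle the matter.

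The unadjusted model also ignores the blocking by UNTA. The design balances the arms within each UNTA, but a comparison without UNTA keeps the between-UNTA variation in its standard error. Its limit is then wider than the design warrants, at some cost in power.

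**Working it through.** **Inputs from the protocol (2.1.6):** SD 2.6 g/kg/day, margin 0.5, expected difference 0, α = 0.05 with z = 1.64 (one-sided), power 80%, 335 per group, 20% dropout, 1,000 children in total. Hence 1,000 × 0.80 / 2 = 400 analysed per arm.

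**Assumptions, not in the protocol:** covariates explain R² = 5–30% of the outcome variance; 10–20% of the variance lies between UNTAs.

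**1. The protocol's own figure.** n = 2 × 2.6² × (1.645 + 0.842)² / 0.5² = 334.4, so 335 per arm. This reproduces the stated number. The rounded z values 1.64 and 0.84 give 332.6.

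**2. What each model needs in order to pass.** The unadjusted SE is 2.6 × √(2/n): 0.201 at 335 per arm and 0.184 at 400. The lower one-sided 95% limit clears −0.5 if the observed difference exceeds −0.5 + 1.645 × SE, which is −0.170 at 335 and −0.198 at 400. The adjusted SE is smaller by the factor √(1 − R²).

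**3. One borderline trial at 335 per arm.** Suppose both models estimate −0.18.
- Unadjusted limit: −0.18 − 1.645 × 0.2009 = −0.510, which fails.
- Adjusted limit: −0.493 at R² = 0.10 and −0.456 at R² = 0.30, which pass.

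**4. How often the verdicts differ.** The two estimates are treated as bivariate normal with correlation √(1 − R²). Each passes if (estimate + 0.5)/SE > 1.645.

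| R² | Opposite verdicts, true difference 0, 335 per arm | Same, 400 per arm | Error at −0.5 if either may pass | Error at −0.5 if both must pass |
|---|---|---|---|---|
| 0.05 | 5.1% | 4.1% | 5.9% | 4.1% |
| 0.10 | 7.3% | 5.8% | 6.3% | 3.7% |
| 0.20 | 10.7% | 8.4% | 6.9% | 3.1% |
| 0.30 | 13.5% | 10.4% | 7.3% | 2.7% |

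Simulation with 200,000 runs per setting agrees (for example 13.4% at R² = 0.30 and 335 per arm). Each model alone holds 5.0%.

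**5. Direction of the disagreement.** At 400 per arm and true difference 0, the adjusted model passes alone in 2.8 of the 4.1 percentage points (R² = 0.05) and in 9.6 of the 10.4 (R² = 0.30).

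**6. Omitting UNTA.** Take 14 sites of 48 children, 336 per arm. The SE that ignores UNTA is 2.6 × √(2/336) = 0.2006, so the threshold is −0.170. With arms balanced within sites, the true SE is 0.2006 × √(1 − between-UNTA share): 0.190 at 10% and 0.179 at 20%.

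| Between-UNTA share | Power without UNTA, Φ(0.170/SE) | Power with UNTA, Φ(0.5/SE − 1.645) | One-sided error without UNTA |
|---|---|---|---|
| 10% | 81.4% | 83.7% | 4.1% |
| 20% | 82.8% | 87.3% | 3.3% |

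Simulation with 6,000 runs gives 80.6% against 82.6%, and 83.3% against 87.6%. Overall, power is about 81–83% without UNTA and 83–88% with it.

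**The case against.** The strongest objection is that the deciding model and its covariates are usual content of a statistical analysis plan, which is not at hand and may settle both. That holds for the covariate list: its absence from the protocol is not a fault, and the adjusted model may well contain UNTA. It does not dispose of the main point, because the protocol is not silent. It commits to two models for every analysis and ranks neither.

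A reader might infer more than the text supports in four ways.

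- **That the trial runs at a 5.9–7.3% error rate.** Those figures need a rule that success in either model is enough, and the protocol states no such rule. Requiring both would lower the error to 2.7–4.1%.
- **That the error should be counted over four analyses, two models in each of two analysis sets.** The ITT and per-protocol pairing is a separate question with its own logic in a non-inferiority trial, so it is not counted here.
- **That omitting UNTA invalidates the unadjusted result or underpowers the trial.** It does neither. The error falls below 5% and power stays above the planned 80%.
- **That Annex 8 changes the primary population.** One cell of its variable list gives the primary objective as "the effectiveness of a reduced dose of RUTF in the management of SAM with edema in children aged 6 to 59 months", whereas section 1.2 has "To assess the effectiveness of a reduced dose of RUTF in the management of SAM in children aged 6 to 59 months", with no restriction to oedema. The main objective and the inclusion criteria (2.1.2) also cover SAM without oedema, and Annex 8 itself allows oedema to be absent. This is an editorial inconsistency, unrelated to the choice of model.

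It is also fair that most disagreement at a true difference of 0 is the adjusted model reaching a correct conclusion that the unadjusted one misses. That is a reason to make the adjusted model decisive, not to leave the choice open.

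**Conclusion.** The point holds as an avoidable ambiguity of moderate size. The protocol gives two co-equal analyses of the primary outcome and no rule for when they disagree. Disagreement on non-inferiority would arise in roughly one trial in 25 to one in 10 at 400 per arm when the doses are equal, for an assumed R² of 5–30%. The protocol gives no figure for R², and the range scales with it. The inflated error is conditional on choosing whichever model passes. The UNTA part is a modest loss of precision, about 2 to 4 percentage points of power under an assumed 10–20% between-UNTA variance, and it errs on the safe side. The sample size needs no change.

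**What to change.** In section 2.3.3, make one analysis decisive:

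- a linear regression of weight-gain velocity on arm, with UNTA and a pre-specified list of admission variables that are already collected, for example age, sex, MUAC, oedema and admission weight. Admission weight is also the denominator of the outcome in Annex 8, so its inclusion should be a deliberate choice;
- non-inferiority judged by the lower one-sided 95% confidence limit for reduced minus standard dose against −0.5 g/kg/day, and not by P < 0.05 for a difference;
- the unadjusted model labelled a sensitivity analysis that cannot change the verdict.

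Separately, as an editorial correction, reconcile the oedema wording of the primary objective in Annex 8 with the main and primary objectives in section 1.2 and the inclusion criteria in 2.1.2.

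The cost is a few sentences, with no new data. Fourteen UNTAs use 13 degrees of freedom out of about 800 analysed children, which is negligible.
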